#### Trial status

As of December 2024, the RCT has not yet been initiated. The first inclusion is expected in March 2025.

#### Process evaluation

Following the RCT, participants who consent to follow-up research will be approached to participate in the process evaluation. A qualitative process evaluation will be conducted to assess the satisfaction and acceptability of SH + and to identify the barriers and support to engagement in and adherence to the intervention. In addition, this evaluation aims to explore opportunities for scaling up the implementation of the SH + program for university students within the mental health system available at the university.

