#### Assessment

Data will be collected through self-report assessments at four times points: *t*_*1*_ (baseline – sent at least 10 days before the SH + to the participants already enrolled), *t*_*2*_ (post-SH+, week-7), *t*_*3*_ (main time point – 3 months after SH+), and *t*_*4*_ (follow-up – 6 months after SH+) with the Castor Electronic Data Capture (EDC) software program [33]. Each assessment will be provided via e-mail with a link to the self-report questionnaire to each participant and can be completed on any device with internet access. The time to complete each assessment is approximately 20–30 min. If an assessment remains incomplete, the participant will receive a maximum of three reminders on days 3, 7, and 10 through various communication channels to encourage retention. The participants will receive IDR 50,000 e-money for each completed assessment, with a maximum of four e-money awards (*t*_*1*_ to *t*_*4*_).

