**Assessments**:							
Sociodemographic		X	X		X	X	X
PHQ-9			X		X	X	X
GAD-7			X		X	X	X
PSS			X		X	X	X
WHODAS 2.0			X		X	X	X
EQ-5D-5L			X		X	X	X
MIMIS			X		X	X	X
PSYCHLOPS			X		X	X	X
CSRI			X		X	X	X
Process evaluation (conducted after *t*_3)_						X	

ECAU: enhanced care as usual; PHQ-9: Patient Health Questionnaire-9; GAD-7: General Anxiety Disorder-7; PSS: Perceived Stress Scale; WHODAS 2.0: WHO Disability Assessment Schedule 2.0; EQ-5D-5L: EuroQol 5 dimensions, 5 levels; PSYCHLOPS: Psychological Outcomes Profiles; MIMIS: Mainz Inventory of Micro-stressors; CSRI: Client Service Receipt Inventory

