#### Primary outcome measure

The primary outcome and end point will be the reduction in psychological distress as measured by the total score on the Patient Health Questionnaire Anxiety and Depression Scale (PHQ-ADS) [35, 36] at three-month follow-up. The PHQ-ADS is the validated combined sum score of the Patient Health Questionnaire (PHQ-9) [29] and the Generalized Anxiety Disorder (GAD-7) questionnaires [37]. Psychological distress, as measured by the PHQ-ADS, will also be collected at one-week and six-month follow-up.

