#### Data analysis

Data will be analysed once all data has been collected; no interim analyses will be performed. However, participants can withdraw from the study or the session anytime without giving a reason.

**Quantitative data (RCT).** An intention-to-treat (ITT) approach will be used to conduct data analysis both in primary and secondary outcomes, and the unit of the analysis is individual. The primary analysis will simultaneously assess the treatment effect on the mean PHQ-ADS total score at each time point. All participants randomized to either group will be analysed, regardless of whether they complete the intervention. The ITT population will consist of all participants randomized to the competing intervention strategies who have at least baseline assessment data available. The main conclusion of the trial will be based on the ITT analysis of the primary outcome (i.e., the effect on the PHQ-ADS score at the three-month follow-up).

Adherence will be defined based on attendance at least three sessions of SH+. A per protocol (PP) approach will be used to test the robustness of the intervention results for all outcomes, which will include only SH+/ECAU participants who attend at least three sessions of the SH + intervention [24]. The attendance of the participants will be recorded by the facilitator(s) of the SH+.

Linear mixed models will be used for the PHQ-ADS (primary outcome) and secondary outcomes to evaluate the treatment effect on all endpoints at t2, t3 and t4, with time as a fixed effect, baseline PHQ-ADS score as a covariate and participants as random effects. A t-test will be used to analyse the differences between the two study arms. Multiple imputation will be used to handle the missing values at 3 months. A sensitivity analysis will be conducted to compare the full sample with the sample that excludes ECAU participants who indicated being exposed to SH + materials.

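### The process evaluation is placed after the RCT in the text but after t3 in Table 1, so interviews about SH+ could precede the six-month assessment

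*Protocol article*

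**What the plan says.** The protocol article gives the timing of the qualitative process evaluation in two places.

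- **Process evaluation section (under Procedure):** "Following the RCT, participants who consent to follow-up research will be approached to participate in the process evaluation". The stated subjects are satisfaction with SH+, its acceptability, what helps or hinders engagement and adherence, and scope for scaling up.
- **Table 1, Assessments block:** the row label begins "Process evaluation (conducted after" and names t3. Its only mark is in the Follow-up 1 (three-month) column, and the t4 column is blank.

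The Assessment section defines t3 as "main time point – 3 months after SH"+ and t4 as "follow-up – 6 months after SH"+. The t4 visit belongs to the trial. Under Primary outcome measure, "Psychological distress, as measured by the PHQ-ADS, will also be collected at one-week and six-month follow-up". Under Data analysis, the linear mixed models are used "to evaluate the treatment effect on all endpoints at t2, t3 and t4". The same section rests the main conclusion on "the effect on the PHQ-ADS score at the three-month follow-up" and sets the incremental cost-effectiveness ratios at t3. It also shows that the process evaluation takes the form of interviews and focus group discussions.

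**The concern.** If the evaluation follows the RCT, no outcome remains to be collected and it cannot influence any trial result. If it follows t3, as Table 1 indicates, some participants may talk at length about SH+, possibly in groups, before they report their six-month outcomes.

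Three features of the design make that order worth avoiding:

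- Participants know their allocation (Randomization section), and all outcomes are self-reported.
- The Discussion accepts that expectations can influence such reports.
- SH+ is itself a group course that includes small group discussions (Intervention section), so a focus group that returns to it has something in common with further contact with the intervention.

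Satisfaction with and adherence to SH+ can be described only by people who were offered it, so the extra contact would probably be uneven between the arms. What is at stake is the between-arm comparison at t4, for the PHQ-ADS and the secondary outcomes. The two statements also leave site staff without a single schedule to follow.

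**Working it through.** There is no planned figure to reproduce. The check is a comparison of the schedule statements, followed by a look at whether the size can be bounded.

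**1. What the text implies.** The article lists four self-report assessments, t1 to t4. The last is t4, which is in the analysis model. After the RCT therefore means after t4, that is, later than six months after SH+.

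**2. What Table 1 implies.** The process evaluation row has one mark, in the sixth column after the row label. In the table header that column is Follow-up 1, three months, t3. The outcome rows (PHQ-9, GAD-7 and the others) have marks under t1, t2, t3 and t4 in the same layout, so the position is not an artefact of text extraction.

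**3. The gap.** t4 minus t3 is 6 − 3 = 3 months. Table 1 allows the interviews to fall anywhere in that interval, and the text excludes it. The article nowhere says that interviews wait for t4.

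**4. Which results are exposed.**

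| Result | Time point | Could contact after t3 affect it? |
|---|---|---|
| Primary PHQ-ADS conclusion | t3 | No |
| Cost-effectiveness ratios | t3 | No |
| PHQ-ADS and secondary outcomes | t2 and t3 | No |
| PHQ-ADS and secondary outcomes | t4 | Yes, if the contact comes before t4 |

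**5. Can the size be bounded?** The shift in the SH+ arm mean at t4 equals the share of that arm interviewed before t4, multiplied by the mean per-person effect of the contact. The article gives neither quantity.

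- *Share.* Assume 10 to 30 SH+ participants are interviewed. Against the 148 per arm in the Sample size section, this is 10/148 = 7% to 30/148 = 20%. If the 50% pilot attrition applied at t4, which the article does not say, 148 × 0.5 = 74 would remain, and the share would be 10/74 = 14% to 30/74 = 41%.
- *Per-person effect.* Unknown in size and sign. For illustration only, an assumed 0.2 SD gives a shift of 0.07 × 0.2 = 0.01 SD at the low end and 0.41 × 0.2 = 0.08 SD at the high end.
- *Scale.* The unadjusted standard error of a two-arm difference with 74 per arm is √(2/74) = 0.16 SD, so the largest illustrative shift is about half of one standard error.

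These figures describe the assumptions. They do not estimate a bias in this trial.

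**The case against.** The strongest reply is that the two statements can both be met. After t3 sets an earliest time and no deadline, so an evaluation held after t4 is also after t3. Table 1 has no column beyond t4, so an activity after the last visit has no cell of its own. This is partly right: Table 1 permits contact before t4 but does not require it. It does not explain why the mark sits at t3, or why the label names t3 when t4 is the last assessment.

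A reader might go further and infer any of the following, none of which the article supports:

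- **That the interviews will precede t4.** The article shows only that they could.
- **That only the SH+ arm is contacted.** The Process evaluation section refers to participants who consent and names no arm. One of its aims, scaling up within the university system, does not depend on having attended SH+. That the contact falls mostly on SH+ is inferred from the other subjects. If controls were included, they could learn about SH+ before t4, and the contamination questions are asked only at the one-week and three-month assessments.
- **That the t4 results are biased.** The interviews are described as gathering views, and nothing says that skills are taught again. Discussing barriers need not raise expectations, so even the direction is open. Participants are unblinded throughout, and what this contact would add to that is unknown.

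It can also be said that a condensed article leaves such detail to the full protocol. That would answer a missing timing, but here the article states two different timings.

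**Conclusion.** The inconsistency is real and minor. The text puts the process evaluation after the RCT, and Table 1 puts it after t3 with t4 unmarked, so interviews and focus groups about SH+ could come before the six-month assessment. That could affect the six-month PHQ-ADS and secondary outcomes, given known allocation, self-report, and contact that probably falls mostly on the SH+ arm. Direction and size cannot be determined from the article, and no numerical bias should be attached to this point. The t3 primary conclusion and the t3 cost-effectiveness ratios stand under either timing.

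The conclusion rests on reading the end of the RCT as the end of t4, which the assessment schedule and the analysis model both support, and on taking the column of the mark in Table 1 at face value.

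**What to change.** Reconcile the Process evaluation section with Table 1, so that the timing is stated once and relative to t4.

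**Preferred:** amend Table 1 to agree with the text. Invite each participant to an interview or focus group only after that participant's t4 questionnaire has been returned or its window has closed. The reminder schedule, whose last reminder is on day 10, offers a natural closing point. This is a schedule correction with no extra data collection. Its cost is that interviewees recall the sessions about three months later than they would just after t3.

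**If the Table 1 timing is intended,** for example to protect recall:

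- Correct the Process evaluation section.
- Record, by arm, who was interviewed or joined a focus group before t4, and when.
- Repeat the t4 analysis without those participants' t4 data, keeping their earlier data in the model.
- Acknowledge the contact when six-month results are interpreted.

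The repeat analysis should remain a sensitivity check. Interviewees are self-selected after randomization, so leaving out their t4 data may itself disturb the comparison. It also costs some precision at t4.

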### Study measures

Below (Table 1) is the schedule of enrolment, intervention, and assessment of the RCT which followed the Standard Protocol Items: Recommendations for Intervention Trials (SPIRIT) [34].

**Table 1 Tab1:** Schedule of enrolment, interventions, and assessments for RCT of SH + within according to SPIRIT

	STUDY PERIOD						
	Enrolment	Screening	Baseline	Randomization	Post-intervention	Follow-up 1 (main endpoint nt)	Follow-up 2
		t_0_	Week 1 (t_1_)		Week 7 (t_2_)	3 months (t_3_)	6 months (t_4_)
**Enrolment**:							
Informed consent	X						
Eligibility screening		X					
Allocation				X			
**Intervention**:							
SH+ & ECAU				↔			
ECAU				↔			
**Assessments**:							
Sociodemographic		X	X		X	X	X
PHQ-9			X		X	X	X
GAD-7			X		X	X	X
PSS			X		X	X	X
WHODAS 2.0			X		X	X	X
EQ-5D-5L			X		X	X	X
MIMIS			X		X	X	X
PSYCHLOPS			X		X	X	X
CSRI			X		X	X	X
Process evaluation (conducted after *t*_3)_						X	

ECAU: enhanced care as usual; PHQ-9: Patient Health Questionnaire-9; GAD-7: General Anxiety Disorder-7; PSS: Perceived Stress Scale; WHODAS 2.0: WHO Disability Assessment Schedule 2.0; EQ-5D-5L: EuroQol 5 dimensions, 5 levels; PSYCHLOPS: Psychological Outcomes Profiles; MIMIS: Mainz Inventory of Micro-stressors; CSRI: Client Service Receipt Inventory

#### Screening measures

The Patient Health Questionnaire-9 (PHQ-9) is used as a screening tool. The PHQ-9 is a self-administered questionnaire consisting of nine items that can be scored from 0 (not at all) to 3 (almost every day) [29]. PHQ-9 score range from 0 to 27 with 0–4 indicating no depressive symptoms, 5–9 mild, 10–14 moderate, 15–19 moderately severe, and 20–27 severe. The PHQ-9 has been validated for Bahasa Indonesia with a Cronbach’s alpha of 0.885 and a cut-off score of 5.5, indicating that people have experienced depression [28].

Indication of imminent risk of suicide or self-harm or other life-threatening risk will be assessed using Suicide Ideation Scale (SIS) which is a 10-item self-report questionnaire to identify ideation that distinguishes covert suicidal ideation from more overt or intense ideation [30]. The SIS scored from 1 (never or none of the time) to 5 (always or a great many times) based on how the participant has felt or behaved in the past week, with a total score range from 10 to 50. The SIS has been validated to Bahasa Indonesia with a Cronbach’s alpha 0.92 and cut-off score ≥ 21.89 [31].

Cognitive impairment will be assessed using an observation checklist from the PM + manual [32].

#### Primary outcome measure

The primary outcome and end point will be the reduction in psychological distress as measured by the total score on the Patient Health Questionnaire Anxiety and Depression Scale (PHQ-ADS) [35, 36] at three-month follow-up. The PHQ-ADS is the validated combined sum score of the Patient Health Questionnaire (PHQ-9) [29] and the Generalized Anxiety Disorder (GAD-7) questionnaires [37]. Psychological distress, as measured by the PHQ-ADS, will also be collected at one-week and six-month follow-up.

#### Secondary outcome measure

All secondary measurements will be collected at one week, three months, and six months post-treatment. Depression symptoms are measured using the PHQ-9 [29]. The PHQ-9 is a self-administered questionnaire consisting of nine items that can be scored from 0 (not at all) to 3 (almost every day), with a total score ranging from 0 to 27. The PHQ-9 has been validated in Bahasa Indonesia demonstrating good internal consistency (Cronbach’s alpha of 0.885), and a cut-off score of 5.5, which indicates that people have symptoms of depression [38].

Anxiety symptoms are measured using the GAD-7 [37]. It consists of seven items with response options ranging from 0 (not at all) to 3 (almost every day), with a total score ranging from 0 to 21. The GAD-7 was translated into Bahasa Indonesia and validated with a Cronbach’s alpha 0.867 and a cut-off score of 6 [39].

The Perceived Stress Scale (PSS) will be used to measure perceived stress. The PSS is a measure of an individual’s perception of recent stress [40]. The items are designed to measure how unpredictable, uncontrollable and overwhelming respondents feel their lives are. The questions in the PSS ask about feelings and thoughts over the past month. The PSS consists of 10 items that are scored from 0 to 4 with the response options being ‘*never*’, ‘*almost never*’, ‘*sometimes*’, ‘*fairly often*’ and ‘*very often*’. The PSS in Bahasa Indonesia showed very good item reliability (0.98) and person reliability (0.79) [41].

General functioning will be measured by the WHO Disability Assessment Schedule 2.0 (WHODAS 2.0) -12 items [42]. The WHODAS 2.0 is a generic assessment tool that can be used to measure health and disability at the population level or in clinical practice. It consists of 12 items that assess six activity domains: understanding and communicating, getting around, self-care, getting along with people, life activities and participation in society. For each item, the participants indicate the level of difficulty (none, mild, moderate, severe, extreme). The Bahasa Indonesia version of WHODAS 2.0–12 items showed good internal consistency (Cronbach’s alpha between 0.634 and 0.853) and test-retest reliability (0.764 and 0.866) [43].

Improvement in Quality of life will be measured by the EQ-5D-5L. The EQ-5D-5L instrument, provided by the EuroQol Group, consists of two sections. The first section includes five items covering five health state dimensions: mobility, self-care, usual activities, pain/discomfort, and anxiety/depression. Each dimension has five response levels: no problems, slight problems, moderate problems, severe problems, and extreme problems/unable to. These responses can be combined into a 5-digit health state profile; for example, ‘11122’ indicates no problems in mobility, self-care, and usual activities, with slight problems in pain/discomfort and anxiety/depression [44]. The second section of the EQ-5D-5L is the visual analogue scale (VAS), where respondents rate their overall health status on a vertical scale from 0 (‘worst imaginable health’) to 100 (‘best imaginable health’). The recall period for both sections of the EQ-5D-5L is ‘today.’ The EQ-5D-5L has been widely used and is available in over 150 languages, including Bahasa Indonesia, and has good test-retest reliability (Gwet’s agreement coefficient: 0.85–0.99 and percentage agreement: 90–99%) [45]. Indonesian’s utility [46] weights are applied to the EQ-5D-5L data, and changes in participants’ quality of life years gained between the intervention and control groups are determined.

We assess resilience, which is defined as the ability to maintain good mental health despite adversity [47]. This involves linking changes in mental health to exposure to stressors. The Mainz Inventory of Micro-stressors (MIMIS), which was recently developed to measure objective micro-stressors of modern life in the last 14 days [48], will be used for this purpose [49]. Each MIMIS item has two response scales: a four-point Likert scale indicating the frequency with which a stressor occurred, ranging from 0 (did not happen/ almost never) to 3 (almost every day), and a five-point Likert scale indicating the extent to which the stressor caused mental strain, ranging from 0 (this situation did not happen) to 4 (severe impact).

The Psychological Outcome Profiles instrument (PSYCHLOPS) assesses self-identified problems [50]. The PSYCHLOPS consists of four questions that cover three domains: problems (two questions), and functioning (one question), and wellbeing (one question). The participants are asked to give free answers to the problem and the functional domain. Responses are scored on a six-point scale, with producing a maximum score of 20. The pre- and post-therapy versions of PSYCHLOPS have the same four questions with additional in the post-therapy version about overall evaluation questions, a self-rated outcome ranging from ‘much better’ to ‘much worse’.

The Client Service Receipt Inventory (CSRI) [51] will be used to examine cost-effectiveness and health service utilization over the eight months (t1, t2, t3, t4). The questionnaire consists of questions concerning what kind of health services (public, private, university, or others), number of visits, type (in-person/ online), duration of contact, travel and waiting time, and travel cost. Additionally, trial costs will be collected (e.g. training, book printing, supervision).

#### Other measures

Sociodemographic information will be collected during screening and at all-time points. Data will be collected on demographics (e.g., gender, age, religion), education (e.g., GPA, year of study, field of study), and living conditions (e.g., housing, living allowance). Contamination questions will be asked at the one-week post-test and the three-month follow-up in both arms. For the intervention group, participants will be asked, ‘Did you discuss SH + with others?’ For the control group, participants will be asked, ‘Did you know about SH+?’ if the answer is ‘yes’, there will be several follow-up questions (e.g., ‘How did you know about SH+’, ‘Did you learn about the SH + such as reading the book or listening to the audio?’).

*Translation and adaptation of the study measures*. PSYCHLOPS, MIMIS, and CSRI were not yet available in Bahasa Indonesia. Therefore, in this project, we adapted these three instruments. In general, the adaptation process included translation, synthesis, back-translation, and final synthesis. The Indonesian research team (DA and [name]) carried out the synthesis part, while hired professionals’ translators did the translation into Bahasa Indonesia and back-translation into English (different translator).

In the adaptation of PSYCHLOPS, there were no changes between the English version and the Bahasa Indonesia version. For the adaptation of MIMIS, we used the result of a qualitative interview with university students (*N* = 30) in Indonesia about their problems. The results of these interviews informed new items related to daily challenges reported by university students in Indonesia, resulting in a version of the MIMIS adapted for Indonesian university students. We adapted the CSRI based on the health system in Indonesia and had a consultation with an expert in health economics.

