#### Contamination

To minimize the risk of contamination, we implemented several measures: During the first session, participants in the SH + group are explicitly asked not to share or discuss the intervention materials with others outside the SH + group. We do not explicitly restrict the control group from independently accessing the SH + materials on the WHO website. Therefore, to know if they were accessing the material, during the T2 and T3 we ask them about whether they knew about the SH+ (see other measures above).

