As common in psychological intervention trials, participants in this study could not be concealed from the treatment allocation for ethical and practical reasons. This may introduce some bias in self-reported outcomes, e.g. the intervention group may report greater improvements due to positive expectations, while the control group may experience disappointment. However, both groups were informed about the intervention and control condition and had access to university mental health facilities. These measures mitigated expectancy effects and reduced potential biases.

In conclusion, this study contributes to the growing body of research on culturally adapted psychological interventions for young adults in low- and middle-income countries. It highlights the importance of tailoring evidence-based interventions to local cultural contexts and specific populations. Future research could explore the potential for hybrid or digital adaptations of SH + to further expand accessibility and evaluate its applicability to other groups facing psychological distress in Indonesia and beyond. By addressing the mental health needs of university students, the APRESIASI project lays a foundation for promoting well-being and academic success across the nation.

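### ECAU contamination is asked at t2 and t3 but not at t4, so control participants first exposed to SH+ after month 3 cannot be identified when the 6-month effect is examined

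*Protocol article*

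**What the plan says.** Two sections fix when contamination is measured, and they agree. Other measures says "Contamination questions will be asked at the one-week post-test and the three-month follow-up in both arms". The Contamination section says of the control group that "during the T2 and T3 we ask them about whether they knew about the SH"+.

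The same Contamination section leaves control access open, with no end date: "We do not explicitly restrict the control group from independently accessing the SH + materials on the WHO website".

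The Assessment section describes t4 as "follow-up – 6 months after SH"+. The Data analysis section uses linear mixed models "to evaluate the treatment effect on all endpoints at t2, t3 and t4", for the primary and the secondary outcomes. It then plans a sensitivity analysis to "compare the full sample with the sample that excludes ECAU participants who indicated being exposed to SH + materials". That sentence names no time point.

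The main conclusion is tied to the PHQ-ADS at three months, and the cost-effectiveness ratios are also set at t3.

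**The concern.** The sponsor treats contamination as important enough for dedicated questions and a sensitivity analysis. Measurement of exposure stops at month 3, while estimation of effects runs to month 6.

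Late exposure is plausible on the protocol's own description. Both arms exist within each university, every SH+ participant receives a copy of the book, the materials are publicly available, and the request not to share them is described only for the first session.

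At stake is how the t4 result is read. If the difference between arms is smaller at t4 than at t3, the benefit may have faded or more of the control arm may have used the material. With no exposure data after t3, the trial would have no information on the second explanation.

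**Working it through.** The point concerns the measurement schedule, so the main check sets the statements side by side. No sample-size figure is involved.

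**Step 1. Coverage by time point**

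| Time point | Effect estimated (Data analysis) | Contamination asked (Other measures; Contamination) |
|---|---|---|
| t2, one week after SH+ | yes | yes |
| t3, 3 months after SH+ | yes | yes |
| t4, 6 months after SH+ | yes | no |

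Exposure is asked at 2 of the 3 time points at which effects are estimated. The uncovered interval is 6 − 3 = 3 months, half of the six months after SH+.

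**Step 2. Could another t4 measure fill the gap?** Table 1 has no row for the contamination questions at any visit, so the schedule rests on the two text statements. The CSRI is collected at t4, but as described it asks about health-service contacts, time and travel, not about use of self-help material. No other t4 measure in the article records SH+ exposure.

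**Step 3. Who is misclassified at t4?** ECAU participants fall into three groups:

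- Never exposed: correctly kept in the restricted sample.
- Exposed by t3 and reporting it: identifiable, and can still be excluded from a t4 analysis.
- First exposed after t3: not identifiable, and kept as unexposed.

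Only the third group is the problem.

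**Step 4. Direction and size.** Let D be the t4 difference without late exposure, c the share of ECAU first exposed after t3, and g the fraction of the SH+ effect that such a person gains. The difference observed is then D × (1 − c × g). The documents give neither c nor g. The values below are assumptions, for illustration only.

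| c | g = 1 (full effect) | g = 0.5 |
|---|---|---|
| 5% | 0.95 D | 0.975 D |
| 10% | 0.90 D | 0.95 D |
| 20% | 0.80 D | 0.90 D |
| 30% | 0.70 D | 0.85 D |

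The g = 1 column is extreme: it credits someone who finds the book or audio alone with the full benefit of a facilitated five-session group course. Whatever the true values, the planned exclusion cannot remove this dilution, because the people causing it are not flagged.

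**The case against.** The strongest reply is that nothing decisive depends on t4. The main conclusion and the cost-effectiveness ratios are set at month 3, and exposure after t3 cannot alter an outcome already measured at t3. This stands, and it makes the point a minor one.

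Three stronger readings are tempting, and the documents do not support them.

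- **That the plan does misclassify participants at t4.** A reader might infer this because effects are estimated at all three time points. The sentence on the sensitivity analysis names no time point, however, and it follows directly on one about missing values at 3 months. A t3-only reading is at least as natural. What can be said is conditional: if the check is applied at t4, it misclassifies.
- **That a known share of exposed controls would be missed.** Assuming a constant exposure rate of 1–5% per month gives 39–43% of those exposed by t4. The figure hardly moves with the rate because it mostly restates how much of the calendar lies after t3. Nothing in the documents supports a constant rate.
- **That the opening control-arm question hides exposure at t2 and t3 as well.** It asks whether the participant knew about SH+, and the item on the book or audio follows only after a yes. But the Discussion says "both groups were informed about the intervention and control condition", and registrants confirmed that they could attend the SH+ sessions. Most should answer yes and reach the direct item. The planned exclusion is in any case of those exposed to the materials, not of those merely aware of them.

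It is also fair to object that excluding controls by self-reported exposure breaks the randomised comparison. A t4 question would therefore inform the reading of a fading effect without settling it. That stands too.

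**Conclusion.** The gap is real and follows from explicit statements: ECAU exposure first occurring between t3 and t4 is not recorded, although effects are estimated at t4 and access to the materials stays open. Because the data would not be collected, an analysis plan that is not shown here could not repair it.

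The consequence is confined to the t4 results. The t3 conclusion and the cost-effectiveness ratios are not affected. The likely direction is dilution of the t4 difference, on the assumption that exposed controls gain some benefit. Its size cannot be estimated from the documents. This is a low-cost improvement to a secondary time point and no threat to the trial's main finding.

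**What to change.** Repeat the existing contamination questions in the t4 online form, asking about the time since t3. In Data analysis, define exposure at each time point from the answers up to that time point, and name the time points at which the contamination sensitivity analysis is run. If the t4 form cannot be changed, state that this analysis applies to t2 and t3 only, and that control exposure after t3 is unknown when the t4 result is reported.

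The cost is a few more items on one questionnaire and a sentence or two of analysis text. Since t4 is the last assessment, asking there cannot prompt exposure that affects a later outcome, provided the items come after the outcome measures. The wording at t2 and t3 is better left as it is: naming the book and audio to every ECAU participant before the primary endpoint could itself create contamination. Even with t4 data, the comparison that excludes exposed controls remains non-randomised and should be reported as such.
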